## **Abstract**

**Design and objective:** This randomized controlled study aims to evaluate an intervention in Malaysia that educates women about breast cancer (BC) screening and navigates them to Clinical Breast Examination (CBE) services and leads to an increase in BC screening uptake whilst taking account of the COVID-19 pandemic context.

**Study population:** Women who are aged 40-74 years, living in Segamat District, Malaysia, with a registered mobile phone number will be sampled randomly from the total population of women who participated in the South East Asian Community Observatory (SEACO) Health Survey (2018). BC patients or women experiencing BC symptoms at the time of recruitment will be excluded. Computer-generated random numbers will be used to assign women randomly to the intervention group (IG) or the comparator group (CG).

**Interventions:** The IG will receive a multi-component mHealth intervention i.e. information about BC will be provided through an educational website, and telephone calls and text messages from community health workers (CHWs) will raise BC awareness and offer to navigate women to CBE services. The usual free opportunistic screening service will be available for CG participants. It will not be possible to 'blind' participants, data collectors and CHWs.

**Outcome measures:** CBE screening uptake is the primary outcome measure and will be recorded by nurses conducting CBEs. Data collectors will use telephone interviews to assess differences in relation to awareness about BC signs/symptoms, intention to attend CBE and mammogram screening, breast self-examination practice and barriers to screening pre- and post-intervention. IG participants will provide an assessment of intervention acceptability and appropriateness.

**Analysis:** A Chi-square test will be used to compare the proportion of participants who attended CBE within 4-6 weeks after the baseline survey in the IG and CG. Multivariate regression analyses will be conducted to investigate between-group differences over time and variable influences on screening participation.

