### **Participant randomization and recruitment**

Women will be selected randomly from the two sub-districts using the SEACO database as the sampling frame and then randomized to the intervention group (IG) or comparator group (CG) with a 1:1 allocation prior to being contacted. Randomisation will be conducted by a SEACO statistician ([name]) using Stata module RANDOMIZE without blocks [34]. Participant enrolment will be conducted by trained SEACO data collectors. All randomly sampled women who were then randomized to the IG or CG will be invited to participate by trained data collectors over the phone. The resources for this study do not permit separation of enrollment and data collection procedures and, so, DCs will be aware which group the women are assigned to and this aspect may increase the risk of bias. Participants and intervention providers will not be blinded during the enrollment and surveys. CHWs will not collect outcome measures. Women who agree to participate will receive an explanatory statement about the study and a token of appreciation for their participation.

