#### ***Surveys (baseline and follow-up)***

The baseline and follow-up surveys will be completed over the phone. Trained SEACO data collectors will conduct telephone surveys with participants from the IG and CG that will take approximately 15-20 minutes. The follow-up survey will take between 20-25 min for the IG and 15-20 min for the CG. The surveys comprise a number of previously adapted and validated questionnaires. In order to ascertain changes in BC symptom recognition, we will include the validated Breast Cancer Awareness Measure for Malaysia (B-CAM-M) [41] before-and-after the intervention implementation. CBE and mammogram screening intentions at baseline will be measured by asking participants to respond to the statement 'I intend to have a Clinical Breast Examination to check for breast cancer in the near future', using a 5-point Likert scale (strongly disagree – strongly agree), providing the option 'I have not yet

thought about this'. Unless participants choose the last option, participants will also be asked at what age they are thinking of getting the CBE [42]. The same questions will be asked about participant's intention to attend mammogram screening. The follow-up survey will also include specific questions to assess participant satisfaction with the screening [43,44] as well as the acceptability and appropriateness of the intervention based on an adapted version of the validated Acceptability E-scale [45] (IG only).

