**IG & CG: Telephone follow-up survey**

SEACO staff will conduct the follow up assessment

**Figure 1.** CENP study flow

**Table 1** Barriers to BC early detection mapped onto the subcomponents of the COM-B model and how the CENP intervention aims to address those (look at <https://implementationscience.biomedcentral.com/track/pdf/10.1186/s13012-018-0821-y.pdf> )

|                                                                                            | Capability                                                                                                                                |                                                                                                                                                                      | Opportunity                                                                                                                                       |                                                                                                                                                                                    | Motivation                                                         |                                                                                           |
|--------------------------------------------------------------------------------------------|--------------------------------------------------------------------------------------------------------------------------------------------------|----------------------------------------------------------------------------------------------------------------------------------------------------------------------|----------------------------------------------------------------------------------------------------------------------------------------------------------|------------------------------------------------------------------------------------------------------------------------------------------------------------------------------------|---------------------------------------------------------------------------|-------------------------------------------------------------------------------------------|

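### Shared staff explain why data collectors know the arm at recruitment, but not why the follow-up caller must; partial masking of the interviewer-collected secondary outcomes is cheap and is not planned.

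*Protocol*

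**What the plan says.** Under *Participant randomization and recruitment*, the protocol assigns recruitment to the survey team: "Participant enrolment will be conducted by trained SEACO data collectors". It gives the constraint, "The resources for this study do not permit separation of enrollment and data collection procedures", and draws the consequence that "DCs will be aware which group the women are assigned to and this aspect may increase the risk of bias". The same section adds: "Participants and intervention providers will not be blinded during the enrollment and surveys". The *Abstract* is broader: "It will not be possible to 'blind' participants, data collectors and CHWs".

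The same staff group handles the surveys. *Surveys (baseline and follow-up)* says: "Trained SEACO data collectors will conduct telephone surveys with participants from the IG and CG". Figure 1 says of the follow-up call only that "SEACO staff will conduct the follow up assessment". Under *Intervention Group*, data collectors also text the campaign link to intervention women after the baseline survey.

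The follow-up interview differs by arm: "The follow-up survey will take between 20-25 min for the IG and 15-20 min for the CG". It contains an acceptability scale marked for the intervention group only, and no order of items is fixed.

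The primary outcome follows another route. Clinic nurses record attendance (*Abstract*; *BC screening attendance*), and the community health workers collect no outcomes.

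**The concern.** The reason given covers less than the conclusion drawn from it. At recruitment and baseline a collector handles arm-specific tasks and can hardly avoid knowing the allocation. Follow-up is a different call, weeks later, and nothing in the protocol requires that caller to have recruited the woman or to see her arm. The protocol describes no step to conceal the arm at that call.

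Symptom recognition, intention, barriers and self-examination are all obtained by telephone interview. A caller who knows which women were educated can prompt, probe or code differently without meaning to. Any such difference adds to the between-arm comparison and cannot be separated from an intervention effect afterwards. Symptom awareness is also one of the two outcomes named in the sample size statement.

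**Working it through.** **1. Who knows the arm, and when**

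| Contact | Who | Does the stated reason explain arm knowledge? |
|---|---|---|
| Recruitment and baseline call | Data collectors | Yes: women are randomised before contact, and enrolment and survey are one task |
| Text with campaign link | Data collectors, intervention group only | Yes: the task itself is arm-specific |
| Follow-up call, four weeks after intervention delivery | Described only as SEACO staff | No: a separate call, with no stated need to see the arm |
| Attendance at clinical breast examination | Clinic nurses | Not applicable: not collected by interviewers |

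The protocol speaks of data collectors in the plural, so passing a woman to a different caller is not ruled out. It gives neither their number nor their languages.

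**2. The plan's own figure**

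*Sampling size and procedure* gives 932 women (466 per arm) for 80% power at the 5% level to detect 9 points. Sidedness is not stated; two-sided is assumed. The formula per arm is

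n = [1.96·√(2p̄(1−p̄)) + 0.8416·√(p₁(1−p₁) + p₂(1−p₂))]² / (p₂−p₁)²

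- Examination uptake, 36% to 45%: (1.3607 + 0.5818)² / 0.0081 = 466 per arm, or 932 in total, an exact match. The 36% is from the 2017 survey under *Quantitative research*; the sample size section names no base rate for uptake.
- Symptom awareness, 65% to 74%: (1.2762 + 0.5454)² / 0.0081 = 410 per arm, or 820 in total. With 466 per arm the power is 84.8%.

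On these figures, the nurse-recorded outcome reproduces the 932. Masking follow-up changes neither the sample size nor the power calculation.

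**3. Illustration of interviewer bias**

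Inputs from the protocol: 466 per arm and 65% awareness. Assumption not in the protocol: arm-aware callers shift recorded awareness by b in favour of the intervention group, while the true effect is zero.

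SE = √(2 × 0.65 × 0.35 / 466) = 0.0312

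Rejection probability = P(|Z + b/SE| > 1.96)

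| Assumed b (points) | b/SE | False-positive rate |
|---|---|---|
| 0 | 0 | 5% |
| 1 | 0.32 | 6% |
| 2 | 0.64 | 10% |
| 3 | 0.96 | 16% |
| 5 | 1.60 | 36% |

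Letting the variance change with the shifted proportion gives 6.2%, 9.9%, 16.3% and 37.1% for 1, 2, 3 and 5 points, so the choice of formula hardly matters.

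**The case against.** The strongest reply is that this is a disclosed choice. The protocol states the limitation, names the bias risk and gives a resource reason; nothing is hidden or contradicted. Call-list allocation and item order often sit in a data-collection manual. The collectors are trained, the questionnaires are previously adapted and validated, and intention is a fixed five-point item, all of which limits an interviewer's influence. This stands as to kind: the point is an improvement to the design and not the discovery of an error. Disclosure does not, however, reduce a bias that could be reduced, and the blanket statement in the *Abstract* remains wider than its justification.

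Several stronger readings are tempting, and the documents do not support them.

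- *The same person recruits and later interviews each woman.* Only the staff group is shared. No section says that one individual makes both calls, so reassignment may already happen in part.
- *Follow-up could be largely masked.* The number of collectors, their languages and the call system are not given. Community health workers are matched across Malay, Cantonese, Hokkien, Tamil and English; if few collectors cover a given language, swapping callers may not work for those women. Intervention women have also spoken with a health worker and may have had an arranged examination, so questions on intention, barriers and self-examination invite disclosure. Symptom recognition, asked first, is best protected.
- *The satisfaction items also reveal the arm.* Only the acceptability scale is clearly marked as intervention-only. Since no order is fixed, it cannot be said that it comes before the outcome items.

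**Conclusion.** The point holds as a low-cost improvement to secondary outcomes. Sharing staff between enrolment and data collection explains arm knowledge at recruitment and baseline; it does not establish that follow-up callers must know the arm. The four groups of interview outcomes are left open to a bias that could be reduced with modest effort.

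A reader might infer that the trial's main result is compromised. It is not: attendance is nurse-recorded and outside this point. Nor does the mention of awareness in the sample size statement carry much weight, since awareness alone would need only 820 women.

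The size of the bias is unknown. The rates of about 10%, 16% and 36% rest on assumed shifts of 2, 3 and 5 points. They show that a shift well below the 9-point target could mislead, not that one will occur. The women's own reporting bias would remain after any masking of callers.

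**What to change.** Amend *Participant randomization and recruitment*, *Surveys (baseline and follow-up)* and the blinding sentence in the *Abstract* so that, at follow-up:

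1. each woman is called, within the existing team and where language coverage allows, by a collector who did not recruit her;
2. the arm is left off the call sheet;
3. the common outcome items are asked in the same order in both arms, symptom recognition first, and saved before the form reveals the arm and opens the intervention-only acceptability items;
4. the collector records whether and at what stage the arm became known.

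The *Abstract* should then say that participants and health workers are unblinded and that follow-up interviewers are masked as far as practicable.

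The cost is some work on call lists and form order, and some loss of rapport with a new caller. The sample size is unchanged. Masking will be partial; the record in step 4 shows how far it succeeded. Where callers cannot be swapped for reasons of language, saving the common items first is still possible.

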### **Intervention**

The evidence synthesis presents a clear narrative with respect to the need to educate rural women about BC screening and the importance of early detection of cancer combined with community navigation to encourage women to attend BC screening. IG and CG participants will be interviewed as baseline and at follow-up four weeks after intervention delivery has been completed.

Women who will be randomized to the IG will receive an intervention consisting of mHealth education and community navigation. Our previous mass media campaign, the Be Cancer Alert Campaign (BCAC), improved BC symptom awareness in Malaysia [10] and the BCAC website, video and brochure will be used to educate women as part of this study. Women face numerous emotional, practical, socio-cultural and health-system related barriers, and most recently, concerns related to the COVID-19 pandemic. We will train local female community health workers (CHWs) who will offer women two-way communication to address their fears and help them navigate the breast health care

system [35]. Additionally, we will train 1-2 male CHWs to engage with a woman's husband or male relatives if a woman communicates to her female CHWs that she would benefit from such engagement. There are a number of health system-related barriers and we will use the family planning clinic ran by the Ministry of Women, Family and Community Development (LPPKN) in Segamat to refer women for free CBE screening. A one-off reimbursement for transportation fees to the clinic will be offered to participants. Due to the COVID-19 pandemic and the MCO in Malaysia, the uptake intervention will be delivered through mHealth. A multi-component mHealth intervention will be used to promote screening and will include a combination of telephone calls and text messages to communicate with, and navigate, participants.

### *Intervention Group*

**Figure 1** demonstrates the intervention flow. Trained data collectors from SEACO will recruit women assigned to the IG via phone call and conduct a baseline survey with women who provide verbal consent to participate in the study. Data collectors will then send women from the IG group a text message that contains the link to the BCAC materials [36]. One CHW will be assigned to support between 50-60 women who agreed to participate. CHWs will call the women they have been assigned to in the same week to discuss BC symptoms and BSE, address any barriers to screening, and ask them whether they are interested in attending a CBE at the LPPKN clinic. If the participants are interested, CBE appointments will be offered to take place the following week at a time that suits the participant. CHW will address concerns of participants who are not interested in screening, but no further action will be taken by the CHW if participants refuse to attend the CBE. Nurses will ask women with normal CBE results to attend screening biannually as recommended in the clinical practice guidelines [37]. Women with abnormal findings during the CBE will see a doctor at the LPPKN clinic who will refer them to a hospital for a mammogram as soon as possible after their CBE, free of charge. Participants will be informed in private about their mammogram results by the LPPKN nurses and CHWs will not be informed of the result. CHWs will call women who do not attend the CBE to identify the reason for non-participation, address further barriers and reschedule the appointment if agreed with the participant. CBE positive women who miss their mammogram appointment will be called by the LPPKN nurses.

### *Recruitment and training of CHW*

We aim to recruit 15-20 CHWs from the two study sub-districts. We will approach women aged 40-74 years from the SEACO community engagement committee (CEC) and ask them to participate as well as to identify other women who might be willing to be trained as a CHW for this study. CHWs will be recruited from different ethnic backgrounds to be matched with up to 60 female participants with the

same ethnic background and mother tongue (Malay, Cantonese, Hokkien, Tamil and English), which has been demonstrated to be more effective in increasing mammography screening uptake [38]. A recent review of CHWs reported that CHW-led interventions were associated with an increase in CBE and mammogram screening rates in 70% of the included research papers [14]. The CHW will be asked to confirm, prior to contacting the matched participants, that they have no pre-existing formal relationship with the participants (e.g. family relationship, teacher-student relationship, etc.), however, the CHW may be friendly with participants who live in the same neighborhood. CHWs will need to be literate, have access to a mobile phone and are able to attend all training sessions. CHWs will be asked to attend five hours of virtual training delivered over five consecutive weeks. A breast cancer surgeon, a public health physician, a staff nurse trained in health communication, a LPPKN nurse and a public health academic will train the CHWs on the basics of BC, CBE and mammogram screening, BSE, communication skills, how to address potential barriers and the importance of confidentiality. CHWs will practice their skills during role play using a prepared calling script to guide the phone conversation with participants. Two male volunteers will also participate in the CHW training and learn to speak to the participant's husbands or male relatives about participating in the study, if requested. Telephone conversations between the CHWs and participants will be recorded as per protocol. CHWs will receive a monthly phone credit and a one-off cash allowance for their time.

### *Comparator Group*

During the recruitment call, participants from the CG will be made aware that BC is the commonest cancer amongst women in Malaysia and about the importance of early detection. Women who will be randomized to the CG will not receive the intervention but may avail of 'usual' screening via their local clinic (subject to pandemic restrictions).

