## **Evaluation**

### *Outcome measurements*

Our primary measure is the difference in CBE screening uptake between women who receive the CHW-led education and navigation intervention and women from the CG who receive usual standard practice (i.e. opportunistic screening at clinics) during the pandemic. In addition to increased awareness about the CBE screening and engagement with the screening programme, secondary outcomes include positive change related to:

- BC symptom recognition
- Intention to attend CBE and mammogram screening
- Beliefs and barriers regarding BC and BC screening
- Practice of breast-self-examination (BSE)
- Mammogram screening attendance (for CBE positive women)

Outcomes related to the programme evaluation are informed by the RE-AIM framework, i.e. reach, effectiveness, adoption, implementation and maintenance [39], together with measures of acceptability, appropriateness and feasibility [40].

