### *BC screening attendance*

LPPKN nurses will be asked to record CBE attendance in a spreadsheet that will be shared with SEACO on a weekly basis. Mammogram attendance will be collected retrospectively from the LPPKN clinic.

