**Train 1-2 male CHWs**

Male CHWs will be trained to provide information for women's husbands/ partners /other male relatives who the women rely on for transport and support.

**CG: Telephone recruitment & baseline survey** (n=466)

SEACO staff will assess and recruit randomly selected women (provide study information, assess eligibility, gain verbal consent, complete baseline survey)

**IG: Telephone recruitment & baseline survey** (n=466)

SEACO staff will assess and recruit women randomized to the intervention group (provide study information, assess eligibility, gain verbal consent, complete baseline survey)

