| Provider level                                                                      | Varying CBE skills                                                                                                                               | Lack of awareness about breast cancer and screening among non-specialists                                                                                            | Time constraints
Understaffed clinics                                                                                                                 | Provider-patient communication
Dominantly male doctors                                                                                                                          |                                                                           | BC screening is not prioritised                                                           |
| Patient level                                                                       | Lack of BSE practice skills                                                                                                                      | Lack of awareness about BC and importance of early detection                                                                                                         | Cost to patient
Transport to clinics
Long waiting times at clinic                                                                                  | Husband are not always supportive                                                                                                                                                  | Low perceived susceptibility                                              | Embarrassment
Fear                                                                     |

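### The comparator is labelled usual opportunistic screening, but its recruitment call adds an early-detection message stated for that arm only

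*Protocol*

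**What the plan says.** The protocol describes the comparator in three places.

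- **Outcome measurements** sets the primary measure, uptake of clinical breast examination (CBE), against "women from the CG who receive usual standard practice (i.e. opportunistic screening at clinics) during the pandemic".
- **Abstract**: "The usual free opportunistic screening service will be available for CG participants".
- **Comparator Group**, on the telephone contact in which women are enrolled: "participants from the CG will be made aware that BC is the commonest cancer amongst women in Malaysia and about the importance of early detection". The same section adds that these women "will not receive the intervention but may avail of 'usual' screening via their local clinic".

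For the intervention group (IG), the Figure 1 box on the recruitment call reads: "SEACO staff will assess and recruit women randomized to the intervention group (provide study information, assess eligibility, gain verbal consent, complete baseline survey". The CG box lists the same four steps. Neither box mentions an early-detection message. Education in the IG comes later, through the campaign text link and a community health worker call "to discuss BC symptoms and BSE, address any barriers to screening".

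Under Participant randomization and recruitment, women are randomised before they are contacted, and the data collectors who enrol and survey them know the arm.

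**The concern.** Opportunistic screening at a clinic does not include a telephone call telling a woman that breast cancer is common and that finding it early matters. The comparator that will be delivered is therefore not the one named in the primary measure.

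The added content is not neutral by the protocol's own account. The Background says that uptake depends on doctors offering screening, on women knowing about the disease and the value of screening and early detection, or on both. The Intervention section bases the programme on the need to teach rural women about these matters. Table 1 lists "Lack of awareness about BC and importance of early detection" as a patient-level barrier. The CG message addresses that barrier in nearly the same terms.

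Two things are at stake:

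- **What the result means.** Statistical analysis plans a difference in uptake and a number needed to treat. Readers will take both as gains over usual care.
- **Comparability at baseline.** As written, the message is an exposure specific to one arm, given in the call that contains the baseline survey. Intention to screen and beliefs about screening are secondary outcomes measured in that survey.

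**Working it through.** **1. The plan's own figure.** Sampling size and procedure gives 466 per arm, 80% power, the 5% level and a 9-point rise. It states no control rate for CBE. The 36% who had received a CBE in the 2017 Segamat survey (Quantitative research) is taken here as an assumption, as is a two-sided test.

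n per arm = [1.960·√(2p̄(1−p̄)) + 0.842·√(p₁(1−p₁) + p₂(1−p₂))]² / (p₂−p₁)²

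With p₁ = 0.36, p₂ = 0.45 and p̄ = 0.405: (1.3607 + 0.5818)² / 0.0081 = 465.8, so 466 per arm. The stated figure is reproduced. For symptom awareness, 65% against 74% needs 410 per arm, and 466 gives 84.8% power. The message makes no stated figure wrong.

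**2. What a prompted comparator could do to uptake.** The protocol gives no effect size for the message. Suppose it lifts CG uptake by c points and leaves the IG at plan. The contrast becomes 9 − c points and the number needed to treat becomes 100/(9 − c).

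Power at 466 per arm = Φ{[(p₂−p₁)·√466 − 1.960·√(2p̄(1−p̄))] / √(p₁(1−p₁) + p₂(1−p₂))}, with p₁ equal to the base rate plus c.

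| Assumed lift c | Contrast | Number needed to treat | Power, base 36% | Power, base 10% | Power, base 5% |
|---|---|---|---|---|---|
| 0 | 9 points | 11.1 | 80% | 97% | 99.7% |
| 1 | 8 points | 12.5 | 70% | 93% | 98% |
| 2 | 7 points | 14.3 | 58% | 84% | 94% |
| 3 | 6 points | 16.7 | 46% | 71% | 83% |

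The lifts and the 5% and 10% base rates are assumptions. The low rates are included because the 36% is shown without a time window, whereas the trial counts attendance about 4–6 weeks after the survey. The direction is the same throughout, towards zero. The loss of power depends strongly on two quantities that the protocol does not give.

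**3. What it could do to change scores.** Statistical analysis compares change between arms. Let the message raise a CG survey answer by m₀ at baseline and m₁ at follow-up. Compared with a CG that received no message:

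- CG change alters by m₁ − m₀.
- The difference in change (IG minus CG) alters by m₀ − m₁.

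Three cases follow:

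- Message read before the baseline items, effect persists (m₀ = m₁): no bias in change, although the CG baseline is raised.
- Message read before the baseline items, effect fades (m₁ < m₀): the difference in change is inflated.
- Message read after the baseline items (m₀ = 0): the difference in change shrinks by m₁.

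The protocol does not fix the order within the call, so the direction is open.

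**4. Which outcomes the message can reach.** As described, it names no symptom, no CBE and no clinic. The powered awareness item is recognition of a breast lump as a symptom, which the message does not teach. An effect on intention, beliefs or uptake is more plausible.

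**The case against.** The strongest reply is that this is a labelling point. The message is disclosed, is brief, and is only a small part of a package that also includes campaign materials, health worker calls, scheduled free CBE, transport reimbursement and rescheduling. The protocol's rapid review found text or email alone ineffective for uptake. That finding does not concern telephone calls, but it lends no support to a large effect from a single statement. Any bias in uptake runs towards zero and cannot create a false benefit. Both arms also complete a telephone survey on breast cancer, which is not usual care either. Order within a call is script detail, and the protocol does not say that the IG call omits the same background.

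Most of this stands, and it rules out three stronger readings that a reader might infer:

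- *That symptom awareness is distorted.* The message does not teach the symptom item.
- *That power falls to a specific figure such as 46%.* That needs an assumed 3-point lift and a 36% base rate that the sample-size section does not name. At base rates of 10% or 5%, the same lift leaves 71% or 83%. In addition, "LPPKN nurses will be asked to record CBE attendance in a spreadsheet", and those nurses work at one family planning clinic, while CG women are directed to their local clinic. A prompted visit might not be counted, so the effect on measured uptake could be nil.
- *That differences in change are inflated.* That needs the message to come before the baseline items and its effect to fade by follow-up. The protocol shows neither.

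The reply does not remove the mismatch between the sections. Nor does it explain why the message is specified for one arm only, in the baseline call, by staff who know the allocation.

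**Conclusion.** The concern holds as a mislabelled comparator and an avoidable arm-specific exposure at baseline. The comparison remains valid, but it is the intervention package against usual screening plus a brief awareness message. Reported as a gain over usual care, the uptake difference and the number needed to treat would be misdescribed.

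Two effects are possible and neither can be sized from the protocol: a rise in CG uptake, which would bias the effect towards zero, and a shift in CG baseline answers on intention and beliefs if the message is read first. The figures for 1–3 point lifts are illustrations, not estimates. The planned 466 per arm is not shown to be wrong on this account.

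The conclusion rests on the text as written, which states the message for the CG and not for the IG recruitment call. If the working scripts already give both arms the same statement after the last baseline item, only the naming of the comparator remains to be corrected.

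**What to change.** Use one recruitment and consent script, identical in both arms, up to the end of the baseline survey. Then choose one of the following:

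1. Take the message out of the CG recruitment call and give it to CG women at the end of their follow-up survey call. The description as usual opportunistic screening can then stand.
2. Keep the message, read it in both arms after the last baseline item, and describe the comparator as a brief awareness message plus usual screening in the Abstract, Comparator Group and Outcome measurements. Report the uptake difference and the number needed to treat against that comparator.

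The cost is a change to the call script and a few sentences of the protocol. It adds no calls, staff or participants. Under option 1, CG women hear the message some weeks later. Under option 2, the trial no longer claims a contrast with pure usual care.
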